## Abstract

**Background:**

Physical activity is a modifiable behavior related to many preventable non-communicable diseases. There is an age-related decline in physical activity levels in young people, which tracks into adulthood. Common interactive technologies such as smartphones, particularly employing immersive features, may enhance the appeal and delivery of interventions to increase levels of physical activity in young people. The primary aim of the Apps for IMproving FITness (AIMFIT) trial is to evaluate the effectiveness of two popular “off-the-shelf” smartphone apps for improving cardiorespiratory fitness in young people.

**Methods/Design:**

A three-arm, parallel, randomized controlled trial will be conducted in Auckland, New Zealand. Fifty-one eligible young people aged 14–17 years will be randomized to one of three conditions: 1) use of an immersive smartphone app, 2) use of a non-immersive app, or 3) usual behavior (control). Both smartphone apps consist of an eight-week training program designed to improve fitness and ability to run 5 km, however, the immersive app features a game-themed design and adds a narrative. Data are collected at baseline and 8 weeks. The primary outcome is cardiorespiratory fitness, assessed as time to complete the one mile run/walk test at 8 weeks. Secondary outcomes are physical activity levels, self-efficacy, enjoyment, psychological need satisfaction, and acceptability and usability of the apps. Analysis using intention to treat principles will be performed using regression models.

**Discussion:**

Despite the proliferation of commercially available smartphone applications, there is a dearth of empirical evidence to support their effectiveness on the targeted health behavior. This pragmatic study will determine the effectiveness of two popular “off-the-shelf” apps as a stand-alone instrument for improving fitness and physical activity among young people. Adherence to app use will not be closely controlled; however, random allocation of participants, a heterogeneous group, and data analysis using intention to treat principles provide internal and external validity to the study. The primary outcome will be objectively assessed with a valid and reliable field-based test, as well as the secondary outcome of physical activity, via accelerometry. If effective, such applications could be used alongside existing interventions to promote fitness and physical activity in this population.

**Trial Registration:**

Australian New Zealand Clinical Trials Registry: ACTRN12613001030763. Registered 16 September 2013.

**Electronic supplementary material:**

The online version of this article (doi:10.1186/s12889-015-1968-y) contains supplementary material, which is available to authorized users.

## Background

Participation in regular physical activity has been associated with better cardiometabolic indices [1–3], skeletal health [4], and cognitive and academic performance [5, 6] in young people (i.e. children and adolescents aged 7–18 years). Conversely, doing little or no physical activity has been related to poor health outcomes [7] and decreased quality of life in adulthood [8], resulting in extended medical care and associated costs [9, 10]. There is an age-related decline in physical activity levels among children aged nine years and older, with the lowest levels among adolescents (particularly females) [11–14]. This decline is important because physical activity patterns have been shown to track from adolescence into adulthood [15–17]. Increasing physical activity in young people therefore is an important public health and research priority [18].

Despite the importance of regular physical activity, young people live in an environment with increased barriers to physical activity and increased options for sedentary leisure activities [19]. Interventions targeting young people to date have met with mixed success regardless of context of delivery (e.g. home-family based, school based). Moreover, they tend to have limited reach and are resource intensive to deliver because they often involve multicomponent interventions (e.g. educational, environmental, policy) and different settings (school, school plus community, family, primary care) [20, 21]. Given their ubiquitous use by young people, mobile phones may offer a viable opportunity to reach this population and deliver interventions aimed at promoting health behaviors, including physical activity. Benefits of mobile health (mHealth) delivery approaches over traditional face-to-face methods are they can be personalized according to participant needs, and intervention content can be provided anywhere/at any time, making them potentially more accessible, scalable, and cost-effective [22, 23].

mHealth systems can be used to make health information and behavior change more appealing and entertaining through gaming [23]. There is scarce evidence on the effectiveness of health video games played on mobile devices, however, video games played on traditional systems have been shown to promote positive health-related outcomes [24, 25]. Adding physical activity to video gaming has been proposed as a strategy to increase physical activity during leisure time [26–28], with greater enjoyment associated with increased energy expenditure during play of active video games [29, 30]. Importantly, engagement, which reflects distraction from the real world, was found to predict enjoyment and, consequently, energy expenditure [29]. One important design feature to engage and sustain use of such games by making them more enjoyable is the presence of a narrative or story [31, 32]. A narrative with immersive properties—i.e. a process in which people are transported into the story—enables the suspension of disbelief, vivid personal experiences, and affection for the characters [32], all of which important in the development of intrinsic motivation [33], a key determinant of physical activity behavior [34]. An immersive narrative has been positively associated to improvements in physical activity self-efficacy in a randomized trial of a health video game to improve children’s diet and physical activity behaviors [35]. Additionally, previous studies demonstrated that a game-themed aerobic game is perceived as more enjoyable than an exercise-themed aerobic game [30, 36]. Given the target population and intervention proposed, these design features are important to consider.

Much of the evidence to date on the effectiveness of mHealth interventions has focused on the use of short-message service (SMS). This research has targeted a wide range of health conditions [37] and a number of systematic reviews support the delivery of SMS interventions to improve a range of health behaviors [38, 39]. There is growing interest in the use of SMS to promote young people’s physical activity [40], however, the utilization of smartphone technologies, including apps, is still in its infancy. Smart phone technology appears to resonate with young people. National surveys conducted in the United States (U.S.) indicate smartphone ownership among young people aged 12–17 has increased from 23 % in 2011 [41] to 37 % in 2012 [42] and is similar across ethnicity and family income. Mobile phone penetration in New Zealand mirrors these data, where household access to mobile phones increased from 74 to 84 % from 2006 to 2013 [43]. Additionally, 58 % of the U.S. young people have downloaded an application (app) to their devices [44].

In recent years there has been a proliferation in the number of ‘off-the-shelf’ apps developed to promote health behaviors. By 2013 there were more than 40 thousand apps available to the general consumer in the U.S. iTunes store health & fitness category [45]. While only approximately half were genuinely healthcare related, this still represents an immense number of apps, the majority targeting physical activity and dietary behaviors. Further, an assessment of their functionality found apps do little more than provide information [45]. Even though content analysis of apps provide preliminary insights on their potential [46, 47], there is a dearth of empirical evidence to support their effectiveness on the targeted health behavior [48, 49], including physical activity [50, 51].

A proposed model for better understanding how an app intervention may influence possible mediators that change physical activity behavior and consequently improve fitness is presented in Fig. 1. It is hypothesized that the app will positively affect mediating variables, such as enjoyment, autonomy, competence, relatedness, and self-efficacy; which in turn would result in physical activity-related changes in fitness. We identified two commercially readily available apps, both designed to promote increases in walking and running, which are physical activity behaviors that contribute to improvements in fitness. Additionally, we are interested in comparing an app designed with an immersive story to an app without story since game-based stories that engage individuals can be used for health behavior change [24, 35] to model behaviors by immersing and capturing attention.

**Fig. 1 Fig1:**
[figure not shown]
Proposed conceptual model and pathway of how use of the apps may influence possible mediators that change physical activity behavior and consequently influence fitness [86]

Therefore, the primary aim of the Apps for IMproving FITness (AIMFIT) trial is to evaluate the effectiveness of two popular ‘off-the-shelf’ smartphone apps for improving cardiorespiratory fitness in young people aged 14–17 years, compared to usual behavior alone (the control). Secondary goals are to determine the effect of the interventions on physical activity levels, self-efficacy, enjoyment, and psychological need satisfaction. Perceptions of usability and acceptability of the apps will also be assessed.

## Methods/design

An eight-week, three-arm parallel randomized controlled trial will be conducted in Auckland, New Zealand with a total of 51 eligible participants. The primary outcome is cardiorespiratory fitness at 8 weeks after randomization. We hypothesize that participants who receive a smartphone app will have greater cardiorespiratory fitness compared to the control group. Secondarily, we hypothesize fitness, physical activity levels, self-efficacy, enjoyment and psychological needs satisfaction will be greater in the immersive app group compared to the non-immersive app group at 8 weeks after randomization. We also expect that recruitment goals will be met, attrition will be low, and that we will be able to collect complete data on at least 80 % (41/51) of participants.

The protocol is in accord with the SPIRIT 2013 statement [52, 53], and the intervention is described according to the CONSORT-EHEALTH checklist [54]. See Additional file 1 for the complete checklist.

### Study sample and recruitment

Eligible participants are English-speaking New Zealand young people aged 14–17 years, living in Auckland, who are owners of an iPod touch® or smartphone running at least Android 2.2 or iOS 6.0, and are able to perform physical activities but do not meet the New Zealand guidelines for regular physical activity [55] (i.e. at least 60 min of moderate to vigorous physical activity each day). Exclusion criteria are a medical condition limiting their ability to exercise safely, previous use or download of the apps of interest, and inability to comply with the study protocol. Only one child per household is eligible to take part.

Several methods are used for participant recruitment including university electronic mailing lists, advertisements in local newspapers, flyers posted in community locations, and visits to high schools to present the study. Even though subgroup analyses of certain demographics or socioeconomic groups is not a goal of this study, to improve access of indigenous and ethnic minority populations to the intervention we visited schools of the greater Auckland area where a large number of Maori and Pacific reside. The criteria for selection were broad in an attempt to include a diverse sample, reduce homogeneity and improve the generalizability of the results.

Interested participants either initiate contact with the research team or their contact details are obtained from sign-up sheets delivered while visiting schools to present the study. During an initial telephone call, interested participants are screened for eligibility [56] and a study information sheet is either posted or emailed. A baseline assessment is scheduled for eligible participants within 4 weeks of the screening call. Parents/caregivers provide written informed consent for their child (14–15), while the child provides written assent. Those aged 16–17 years provide their own written informed consent. Participants will receive a NZ $30 gift card to a local shopping center as an incentive for participation and encourage completion of study measures. Incentives are not conditional on usage of the app. Moreover, participants will be told both apps will be provided (i.e. free of charge) at study termination, which is particularly important to meet the expectations of using physical-activity related apps of those in the control group in order to avoid high dropout rates. As adherence to the intervention is one of the outcomes of interest, no reinforcement strategies will be used to influence compliance.

### Outcome assessments

Assessments are conducted at baseline and 8-week post randomization (see Fig. 2) at the University of Auckland clinics and sport grounds (duration 45 to 60 min, of which 10 to 15 min to complete self-reported measures). Baseline assessments involve an explanation of study procedures, signed consent and collection of participant-reported secondary outcomes, followed by physical measurements (height and weight) and a field test of cardiorespiratory fitness. Participants are then asked to wear an accelerometer for seven consecutive days. Randomization takes place at a subsequent visit to the participants’ home once baseline accelerometer data collection is completed.

**Fig. 2 Fig2:**
[figure not shown]
Flow diagram of the study. Legend: PAQA-Physical Activity Questionnaire for Adolescents, PACES-Physical Activity Enjoyment Scale, PNSES-Psychological Need Satisfaction in Exercise Scale, PASES-Physical Activity Self-Efficacy Scale

### Ethical approval

Ethical approval was obtained from the University of Auckland Human Participants Ethics Committee (10054/2013). The study was registered at the Australian New Zealand Clinical Trials Registry before commencement (ACTRN12613001030763). Adverse events are collected at each visit or voluntarily reported by contacting the investigator.

### Sample size

A total sample of 51 participants (17 per group) will provide 80 % power at 5 % level of significance (two-sided) to detect a minimal difference of 17 s in time to complete the one mile run/walk test at 8-week post randomization between the treatment groups. This has assumed a standard deviation of 15 s on the primary outcome, with adjustment for multiple comparisons. Based on normative data [57] for this population, the calculation assumes a mean baseline value of 10-min to complete the one mile/1.6 Km run/walk test. An improvement in the completion time of 78 s for this distance corresponds to a shift from the 25^th^ to the 50^th^ percentile in terms of cardiorespiratory fitness, which is considered a meaningful impact towards a more favorable cardiovascular profile.

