
### Statistical analyses

Treatment evaluation will be performed on the principle of intention to treat. Statistical analyses will be conducted using SAS version 9.3 software (SAS Institute, Cary, NC, USA). All statistical tests will be two-sided and maintained at a 5 % significance level. Apart from accelerometry, study data will be keyed into an Excel database using data forms enabled with validation criteria. An assistant will randomly check 30 % of the keyed data for accuracy. All data will be imported into SAS for final analysis.

Baseline characteristics of all randomized participants will be presented for each group using descriptive statistics. Continuous variables will be reported as numbers of observed and missing values, mean, standard deviation, median and range. Categorical variables will be described as frequencies and percentages.

Analysis of covariance (ANCOVA) regression model will be used to evaluate the main treatment effects on the primary outcome, adjusting for its baseline measure, sex, and important baseline confounding factors. Normality of the continuous outcome data will be tested, and the goodness of model fit will be evaluated. Model-adjusted means will be estimated for each group, and their differences will be tested. A similar approach will be used for other continuous secondary outcomes. Generalized linear models will be applied to categorical outcomes as appropriate. Sensitivity analysis will be conducted on the primary outcome with missing data (if >10 %), using multiple imputations with the MCMC method [82].

Psychosocial variables (i.e. perceived enjoyment, autonomy, competence, relatedness and self-efficacy) related to physical activity will be considered as potential mediators of the intervention (Fig. 5 illustrates the mediation model to be tested; dotted lines indicate hypothesized mediation paths) [83]. The recommendations of Kraemer for testing mediators of intervention effects in randomized clinical trials will be followed [83]. Data permitting, further analyses will evaluate the treatment effects on a subgroup of participants who report having adhered to the intervention.

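### The sample-size paragraph contradicts itself: an SD of 15 s cannot be squared with its 78 s gap between the 25th and 50th percentiles, so the stated 80 % power for 17 s is unsupported

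*Protocol article*

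**What the plan says.** The Sample size section of the protocol article makes these statements:

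- On size, power and level: "A total sample of 51 participants (17 per group) will provide 80 % power at 5 % level of significance (two-sided").
- On the target: the trial is sized "to detect a minimal difference of 17 s in time to complete the one mile run/walk test" at 8 weeks.
- On spread and multiplicity: "This has assumed a standard deviation of 15 s on the primary outcome, with adjustment for multiple comparisons". No source is given for the 15 s, and neither the adjustment method nor the number of comparisons is named.
- On the population: from normative data, "the calculation assumes a mean baseline value of 10-min to complete the one mile/1.6 Km run/walk test".
- On the percentiles: "An improvement in the completion time of 78 s for this distance corresponds to a shift from the" 25th to the 50th percentile of fitness.

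The Abstract defines the primary outcome as one-mile time at 8 weeks. The Statistical analyses section plans an ANCOVA adjusted for baseline time, sex and other baseline factors. It gives no baseline-to-follow-up correlation. The opening of Methods/design expects complete data on at least 41 of 51 participants.

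**The concern.** The paragraph contains two statements about how much mile times vary. One is explicit: an SD of 15 s. The other is implicit: a quarter of the distribution spans 78 s. If both described the same quantity, 78 s would be 78 / 15 = 5.2 SDs, whereas the 25th and 50th percentiles of a normal distribution lie about two-thirds of an SD apart.

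The SD drives the sample size. If the spread implied by the percentiles is nearer the truth, the design does not have the power stated for its primary outcome. A reader who takes 80 % power for 17 s at face value would give a non-significant result more weight against a 17 s benefit than it can bear.

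**Working it through.** **1. Inputs.** From Sample size: difference 17 s, SD 15 s, n = 17 per group, two-sided 5 %, power 80 %, percentile gap 78 s. From Statistical analyses: ANCOVA on baseline. Assumed here, because the article does not say: three pairwise comparisons, and a range for the baseline-to-week-8 correlation r.

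**2. Reproducing the plan's figure.** The noncentrality is 17 / (15 × √(2/17)) = 17 / 5.145 = 3.304. With pooled error df = 48 and the Tukey critical value 2.418, power is 80.8 %. With Bonferroni for three pairs (alpha 0.0167), the normal formula gives n = 2 × (2.394 + 0.842)² × 15² / 17² = 16.3, so 17 per group; power by the t distribution with 48 df is 79.1 %. The calculation is sound, and 15 s is the SD that was used.

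**3. SD implied by the percentiles.** Under normality the gap between the 25th and 50th percentiles is 0.6745 SD.

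- Implied SD = 78 / 0.6745 = 115.6 s.
- Ratio to the assumed SD = 115.6 / 15 = 7.7.
- Gap that an SD of 15 s would give = 0.6745 × 15 = 10.1 s.

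**4. Can baseline adjustment bridge this?** The ANCOVA residual SD is SD × √(1 − r²). Setting it to 15 s gives r = √(1 − (15/115.6)²) = 0.992. For an SD of change, SD × √(2(1 − r)), the answer is also r = 1 − (15/115.6)²/2 = 0.992. If the sample SD were half the implied one (57.8 s, an illustrative assumption), a residual SD of 15 s would need r = √(1 − (15/57.8)²) = 0.966.

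**5. Power for 17 s** (17 per group, Tukey, 48 df):

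| r | Residual SD, from 115.6 s | Power | Residual SD, from 57.8 s | Power |
|---|---|---|---|---|
| 0 | 115.6 s | 3.0 % | 57.8 s | 6.7 % |
| 0.8 | 69.4 s | 5.1 % | 34.7 s | 17.1 % |
| 0.9 | 50.4 s | 8.4 % | 25.2 s | 33.5 % |
| 0.95 | 36.1 s | 15.8 % | 18.1 s | 62.9 % |

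**6. Difference detectable with 80 % power** (SD 115.6 s, Tukey). The formula is k × residual SD × √(2/n), where k is the noncentrality giving 80 % power: 3.273 for n = 17 (48 df), and 3.296 for 41/3 = 13.67 per group (38 df).

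| r | Residual SD | 51 analysed | 41 analysed |
|---|---|---|---|
| 0.7 | 82.6 s | 93 s | 104 s |
| 0.8 | 69.4 s | 78 s | 88 s |
| 0.9 | 50.4 s | 57 s | 64 s |

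For example, 3.273 × 69.4 × √(2/17) = 77.9 s.

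**The case against.** The best defence is that the arithmetic is correct and the dispute is only about an assumption. That is so: the fault lies in the SD, not in the calculation. But the conflicting figure stands in the same paragraph and is tied there to the trial's own population, so this is an inconsistency and not merely a different preference.

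A second defence is that the trial sample may vary less than the norms. It enrols only 14–17-year-olds who do not meet the activity guidelines, the article does not say whether the percentiles are sex- or age-specific, and the model adjusts for sex. This stands as a reason not to quote a single true power. It does not rescue 15 s: halving the SD still requires r of about 0.97, and the article states no r and nowhere describes 15 s as a residual or change SD. It calls it the SD on the primary outcome.

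A third defence is skewness. A lognormal shape with a median of 600 s and a slower quartile of 678 s has log-SD ln(678/600) / 0.6745 = 0.181 and an SD of about 111 s, close to 116 s.

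Three stronger readings are tempting, and the documents do not support them:

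- *Power is really 3–16 %.* That range depends on normality, the normative spread and an undocumented r up to 0.95. A narrower sample gives more.
- *A significant 17 s would be called effective.* At an SD of 116 s the smallest significant difference, 2.418 × residual SD × √(2/17), is about 96 s at r = 0 and 30 s at r = 0.95, so an observed 17 s would not be significant.
- *The trial should be powered for, or its confidence intervals judged against, 78 s.* The paragraph calls 78 s a meaningful percentile shift. It never makes it a between-group margin, and sizing a trial for a smaller difference is a design choice.

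**Conclusion.** The inconsistency stands. No part of the article reconciles an SD of 15 s with a 78 s gap between the 25th and 50th percentiles, and baseline adjustment does so only at a correlation of about 0.99. The claim of 80 % power for 17 s is unsupported as written.

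How far the true power falls short cannot be fixed from the article. If times are roughly normal and the normative spread applies, it is between about 3 % and 16 % for r from 0 to 0.95. If the sample's SD is half that, it is between about 7 % and 63 % over the same r. All these figures use 17 analysed per group and Tukey adjustment for three comparisons; fewer completers would lower them. The article sets no rule that a null result excludes 17 s, so misreading such a result is a risk to guard against and not something the plan prescribes.

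**What to change.** In the Sample size section:

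1. Replace the 15 s SD with one consistent with the cited percentiles, or give its source and explain how it fits the 78 s gap.
2. State the baseline-to-week-8 correlation assumed for the ANCOVA.
3. Withdraw the statement of 80 % power for 17 s. Report instead the detectable difference as a range under stated assumptions, for 51 analysed and for the 41 complete cases expected as a minimum, as in the second table above.
4. Add that a non-significant result should not be read as ruling out a 17 s benefit.

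The Trial status section says follow-up is complete and analysis is under way, so the sample cannot usefully change, and none of this asks for more participants. The cost is some rewording and a less favourable stated figure.
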